## Abstract

**Introduction:**

Volunteer support for patients and families at the end of life provides many benefits for the beneficiaries. New technologies could be a necessary resource in the accompaniment although, if there is little literature on palliative care volunteering in general, specifically on volunteering and new technologies, we find little information on the subject.

Therefore, the aim of this study is to implement and evaluate a training program for palliative care volunteers using new technologies in order to begin accompanying patients and families in hospital or at home.

**Methods and analysis:**

A mixed-method study design will be conducted. We will recruit 20 volunteers and 70 patients in two years. Intervention: training of volunteers in new technologies and volunteer accompaniment of patients/relatives using technologies. The control group will accompany patients as usual.

**Ethics and dissemination:**

Ethics approval for the ITV-Pal Programme project was granted by the Malaga Regional Research Ethics Committee. As new knowledge is gained from this project, findings will be disseminated through publications, presentations and feedback to clinicians who are participating in this study.

**Trial registration number:**

NCT04900103.

STRENGTHS AND LIMITATIONS OF THIS STUDYThe use of a mixed model that combines qualitative and quantitative methodology is the best way to evaluate the implementation of a new service, which is why it will be the one chosen in this study.One of the limitations of the study is the effect of the intervention on recruitment and that this may result in different recruitment rates.The main risk of this study is that we will not be able to attend to the different needs of the patients/families, although we will try to offer volunteers who can provide a better response to these needs.

## Introduction

How we care for the dying is perhaps the most pressing personal, social and public health issue of the 21st century. The experience of dying as an integral and acknowledged part of individual life, supported by the very best personalised care, is currently far from being standard practice in Europe and beyond.^1^ Furthermore, it is estimated that by 2050, one in five people in the world will be over the age of 60^1^ with an estimated 52 million people expected to die worldwide in 2030 from chronic diseases such as cancer, cardiovascular and renal diseases and others.^2^ This poses a new challenge to the functional capacity and organisational structures of current healthcare systems.

Distress at the end of life is significantly associated with both physical/somatic and non-physical symptoms. For this reason, patient care cannot focus only on treating physical symptoms through medication. When a terminal illness disrupts a life, it leads to the loss of important relationships, as well as changing the structure of the patient’s social network and the levels of relationship and support.^2^ Dying is, therefore, also a social process.^3^ The psychological distress due to feelings of anxiety, depression, loneliness and being a burden requires additional approaches to care.^4 5^ Approaches that aim to provide supplementary, informal, lay support for patients dying at home, and their relatives, may introduce a valuable sense of ‘community’ and lead to important improvements in the care of the dying. Volunteer support represents an important and necessary community resource for patients and relatives to enhance the experience of living at the end of life and dying.^4 5^ Although few studies exist, those few agree on the beneficial aspects of volunteering on patient and family satisfaction at the end of life.^4 5^

It is of paramount importance to develop innovative, economically viable interventions to support the care that dying patients and their relatives receive. In this way, the current health emergency situation and the confinement has revealed the isolation and loneliness that certain groups have already experienced for a long time, such as the elderly, immigrants or patients and caregivers.^6^ New technologies (NT) may become a useful resource in this kind of situation and have already proven a benefit in the context of palliative care (PC). Healthcare professionals (HCPs) use information and communication technologies to facilitate health services for patients who have problems with access to the services, any disability which restricts movement or who live in a rural area.^7 8^ In some studies, they found that the use of NT in consultation was as effective as face to face.^9–13^ It was even more positive for caregivers, reducing their anxiety and increasing their quality of life.^14^ In this context, the implementation of services that combine volunteer support and NT can be an innovative, economically viable intervention to support the care of dying patients and their relatives. In addition, these approaches bring volunteering closer to people who would like to offer their help but have little time or cannot be in the same place as the patient/relatives. In these cases, virtual volunteering could be a way to reach a larger population.^15^

Studies related to volunteering with NT mainly address the challenges of bringing these types of devices closer to the older population^16 17^ or how volunteers perceive them as another resource to improve their relationship with the caregivers of patients,^18^ but even so organisations are far from including such resources in their practice.

Technologies resources facilitate volunteer interaction and communication with the community, which is increasingly dependent on NT. Furthermore, volunteers with NT training will be able to help patients with daily practical tasks. NTs have also proven useful for therapeutic interventions. The patient can use them to review their biography, maintain social relationships with people who live far away or help them to build a legacy for their loved ones.^19 20^

Although volunteers contribute many hours to accompanying and supporting patients and their relatives, the review of bibliography found no sufficiently robust studies to merit inclusion, and even less when associating PC volunteering and NT. More research is needed to assess the impact of training and support of volunteers in PC. This study aims to analyse the technophobia (fear or aversion towards NT or complex devices) and technophilia (opposed to technophobia and is responsible for establishing the behaviour of adherence, often uncritically, to technological innovations) of patients, relatives, volunteers and health professionals. Once their knowledge of new NT has been assessed, a training programme for volunteers will be evaluated and a programme of accompaniment through technological devices will be implemented.

The aim of this study will be to evaluate the implementation of a volunteer training programme in the use of NT (specifically through smartphones and tablets) to support patients facing a life-threatening illness and their relatives. The specific objectives will be: (1) to explore the need and usefulness of NT from the point of view of patients, relatives, volunteers and HCP in PC and describe their technological profile; (2) to design a tech-volunteer curriculum and implement a tech-volunteer training programme and (3) to implement the tech-volunteer programme within a PC Home care service and Inpatient unit and assess its impact on the care provided.

## Methodology

The Research Ethical Committee of Málaga (25 February 2021) approved this study.

### Study design

The best approach to evaluate the implementation process is through mixed-method and the combination of quantitative and qualitative methods.^21^ Basic quantitative measures of implementation may be combined with in-depth qualitative data to provide detailed understanding of intervention functioning on a small scale. Quantitative methods will measure key process variables and allow testing of prehypothesised mechanisms of impact and contextual moderators. Qualitative methods will capture emerging changes in implementation, experiences of the intervention and unanticipated or complex causal pathways, as well as generating a new theory.

#### A: Quantitative approach

Pragmatic cluster randomised clinical trial to test efficacy (the unit of randomisation is the volunteer and the unit of analysis is the patient/relatives). A pragmatic cluster randomised controlled trial has shown to be the most appropriate design when the programmes are more focused on the organisational level.^22 23^ For our study, the cluster design is based on two levels: the higher or second level is represented by the volunteer (over volunteer the intervention is conducted, ITVPal Programme: Tech-Volunteer Programme in Palliative Care Services), and the lower or first level being represented by the patients/relatives, who have agreed to participate and are going to receive the tech-volunteer care from volunteers of ITVPal Programme.Before-and-after design for satisfaction of volunteers and HPC with the intervention and its implementation to test effectiveness. The design involves evaluating the effects of a deliberate intervention (introduction of ITVPal Programme) by comparing the outcomes of study participants investigated before the intervention with those measured afterwards.Cost–utility study from the perspective of the funder with a time horizon of 2 years. A detailed cost analysis including costs for the adaptation of a volunteer standard course to an ITVPal Programme as well as the recruitment and training costs of the volunteers will be performed.

#### B: Qualitative approach

Interviews (individuals and groups) with HCP, volunteers and with key informants of patients/relatives to test at the beginning the need and usefulness of NT, and also during the implementation process to test changes and experiences. A narrative approach will be adopted, facilitating the production of ‘rich’ data regarding how participants make ‘sense’ of and engage with the ITVPal programme. These interviews will explore the thoughts and feelings engendered by access to this service, initial motivations, as well as thoughts and feelings about care delivery as a whole. Narrative interviewing enables the participants to tell their ‘stories’, prompted by an open question.

### Settings

The study will be conducted in a palliative care unit from both a home care and an inpatient unit of the CUDECA foundation.

The hospitalisation unit is a small hospice consisting of 10 rooms where patients at the end of life are cared for in cases of uncontrolled symptoms, for family respite or in their final days, among other situations. In this unit, volunteers come every afternoon to the rooms where they wish to offer accompaniment to patients and their relatives.

In addition, CUDECA foundation provides home care to more than 1500 patients a year through 7 care teams made up of a doctor, nurse, psychologist and social worker. In these cases, the volunteer accompanies patients and relatives who wish them to do so.

### Participants

A total of 140 patients and/or relatives will be selected from the home care and inpatient unit of CUDECA foundation where the ITV-Pal programme will be implemented. This sample size is enough to detect a mean difference of 3 in the HAD scores between groups of 25%, with a power of 80% and a confidence level of 95%.^24^ Sample size was adjusted according to the standard criteria for cluster randomised trials, using the design effect (DE) of 1.3. The DE was calculated as follows: DE=1+(nc–1)×ICC (where nc is the mean number of individuals in the cluster and ICC the intracluster correlation coefficient). The ICC in the present work was considered to be 0.05 and the mean cluster size was assumed to be 7. A potential loss of 20% was estimated. Therefore, 140 patients/relatives and 20 volunteers are required.

The inclusion criteria will be: patients and relatives cared for by a specialised PC team; to be over 18 years of age; consenting to participate in the study by signing the informed consent form. Subjects who have specific conditions reducing their physical ability to use the devices, for example, visual, hearing or motor impairments will be excluded from the study.

The HCP involved in these services will be included to measure the success of implementing the programme.

The inclusion criteria for volunteers will be an interview with the Volunteer Department and having completed basic care training to be able to carry out their work. Also, a commitment to participate in the study for 1 year. For this reason, more volunteers will be trained as needed during the 2 years of implementation.

### Randomisation

The radomisation will take place in the higher or second level represented by the volunteer (over volunteer the intervention is conducted: ITVPal Programme) using a block randomisation technique. Each block is formed by four volunteers among whom the two study arms will be uniformly distributed. Once the blocks have been created, they will be distributed using a sequence of random numbers and the final list of volunteers allocations will be created. The final list of volunteers allocations will be guarded by the principal investigator of the project, and he will inform the allocation of each volunteer included in the trial.

### Patient and public involvement

The design of this protocol did not involve patients.

#### Intervention

A complex intervention will be carried out in two phases.

First phase: training of volunteers in NT. Volunteers will be trained in the use of NT and their interconnectivity as tools to support their work as volunteers.The topics that will be covered in the volunteer training are the role of the volunteer, use of NT, communication strategies, complicated situations, self-care, summary and closure of the training. All of this is divided into 10 sessions, each lasting approximately 3 hours. This training will be integrated into the specific training programme for PC care volunteers.The control group, on the other hand, will receive the standard training that the care volunteers have received so far.Second phase: volunteer accompaniment of patients/relatives. During the activities carried out by the volunteer with the patient for accompaniment and leisure. It will have the support of a technological device to be used according to the needs of the patient/relatives (eg, internet searches on a topic of interest, video calls, phone calls, virtual visits) It will be an outcome of the study to know what the device has been used for.The control group will accompany patients without using the NT as usual.

### Variables

Sociodemographic variables such as date of birth, gender, educational level, nationality, spiritual beliefs and employment status will be assessed in all groups.

Specifically, relatives will be asked about their relationship with the patient. Volunteers will be questioned about their time of collaboration and whether they have had personal experience with palliative patients and finally, health professionals will be asked specifically about their work experience in PC.

In the following section, the different tools of assessment that each group will have to complete will be indicated:

#### Patients

The ICECAP Supportive Care Measure (ICECAP-SCM) 25 has been developed as a tool for use in economic evaluation conducted in an end of life setting for patients. The questionnaire covers the attributes of: choice, love and affection, physical suffering, emotional suffering, dignity, being supported and preparation with the lowest score being 1 and the highest score being 4.EuroQol-5D-5L,^26^ a generic, brief and easy-to-use questionnaire designed to describe and assess the current health-related quality of life of the person completing the questionnaire. Primary outcome: The descriptive system comprises five dimensions: mobility, self-care, usual activities, pain/discomfort and anxiety/depression. Each dimension has five levels: no problems, slight problems, moderate problems, severe problems and extreme problems. The patient is asked to indicate his/her health state by ticking the box next to the most appropriate statement in each of the five dimensions.Distress thermometer^27^ was developed as a simple tool to effectively screen for symptoms of distress. The instrument is a self-reported tool using a 0–10 rating scale.Edmonton Symptom Assessment Questionnaire^28^ used to rate the intensity of nine common symptoms experienced by cancer patients, including pain, tiredness, nausea, depression, anxiety, drowsiness, appetite, well-being and shortness of breath where 0 is that the symptomatology does not affect him/her at the moment and 10 with the highest intensity.Tech-PH^29^
an instrument for measuring older people’s attitudes toward technology: It was created from the six items in the two factors, techEnthusiasm and techAnxiety. TechPH could be interpreted on a five-point response scale, ranging from 1 (fully disagree) to 5 (fully agree), where the higher the index indicates a higher level of technophilia.The Questionnaire on the Frequency of and Satisfaction with Social Support (QFSSS)^30^ was designed to assess the frequency and degree of satisfaction with perceived social support from different sources in relation to three types of support: emotional, informational and instrumental. Both frequency and satisfaction are measured on a Likert scale of 1–5.Hospital Anxiety and Depression Scale (HADS)^31^ instrument to measure anxiety and depression in a general medical population of patients. The lowest score being 0 and the highest score being 3.

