### Data analysis

#### Quantitative data

Intention-to-treat principle: Descriptive statistics will be used to summarise subject characteristics (age, gender, education, religion, socioeconomic status, marital status, place of residence) and the process evaluation. Basal comparison between groups for independent samples: Student’s t-test or χ^2^ test; for related samples: analysis of variance for repeated measures to analyse changes within groups. Multilevel analysis will be used for main and secondary outcomes. A multilevel modelling approach will be used to examine the difference in the primary endpoint between patients/relatives, taking account of clustering effects at volunteers level. All statistical tests will be two sided and considered significant if p<0.05. Repeated measurements of analyses of variance will be conducted to assess the development of endpoints over time. Multivariate Imputation will be used to handle missing data.

Also, outcome data will be collected for patients and relatives: the cost-effectiveness of care of dying patients, including the volunteer training programme, will be assessed by calculating the incremental cost-effectiveness ratio (ICER). The ICER is defined as the difference in total healthcare costs in the intervention group (including the costs of performing the intervention) compared with the total costs in the control group, divided by the difference in outcomes.^36^ Outcomes will also be measured as QALYs using the EQ-5D health-related quality of life questionnaire. We will also use the capabilities approach (ICECAP). The potential impact of the programme beyond the trial period will be extrapolated using modelling techniques.

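### The only outcome labelled primary is the EQ-5D-5L descriptive system, but the sample size of 140 and its 80% power are built on a HADS difference

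*Protocol article*

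**What the plan says.** Three sections of the protocol article bear on the primary outcome.

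- **Variables, Patients.** Inside the EQ-5D-5L entry stands "Primary outcome: The descriptive system comprises five dimensions: mobility, self-care, usual activities, pain/discomfort and anxiety/depression". Each dimension has five levels. No other measure in the article carries a primary label. HADS comes last in the same list and appears again among the relatives' measures, without the label in either place.
- **Participants.** The sample size is justified on HADS: "This sample size is enough to detect a mean difference of 3 in the HAD scores between groups of 25" (the 25 is a percentage), "with a power of 80% and a confidence level of 95" (also a percentage). It is then inflated for clustering and for 20% loss, giving 140 patients/relatives and 20 volunteers.
- **Data analysis, Quantitative data.** "A multilevel modelling approach will be used to examine the difference in the primary endpoint between patients/relatives", allowing for clustering by volunteer. The endpoint is singular and is not named. The EQ-5D is mentioned here only as the source of QALYs, and the Cost–utility ratio section calls that objective exploratory.

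**The concern.** The primary outcome decides what counts as success, and the sample size should be justified for that outcome. Here the label and the justification point to different instruments, and the analysis section does not settle which is meant. An analysis plan written later could choose either one and cite this article in support.

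The labelled outcome also cannot be tested as it stands. A descriptive system of five ordinal items is not one number per person, so the label alone does not define a difference between arms. The article gives no effect size, SD or power for the EQ-5D-5L. A reader who takes the label at face value would credit it with 80% power that was worked out for something else.

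**Working it through.** **Inputs from the article**

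- HADS difference of 3 points and 80% power (Participants).
- Test level: "All statistical tests will be two sided and considered significant if p<0.05" (Quantitative data).
- Clustering: "Sample size was adjusted according to the standard criteria for cluster randomised trials, using the design effect (DE) of 1.3"; "The ICC in the present work was considered to be 0.05 and the mean cluster size was assumed to be 7" (Participants).
- Loss of 20%, total of 140, 20 volunteers (Participants).
- Two arms balanced within blocks of four volunteers, so 1:1 (Randomisation).
- SD of HADS: not stated, so it is treated as an assumption below.

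**1. Reproducing the plan's own figures.** The design effect is 1 + (7 − 1) × 0.05 = 1.30, as stated. The total is 20 × 7 = 140, as stated. Without an SD, the step from 3 points to 140 cannot be reproduced from the article alone, so it is worked in both directions.

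**2. Effective size.** Evaluable: 140 × 0.8 = 112. Allowing for clustering: 112 / 1.3 = 86.2. Per arm: 86.2 / 2 = 43.1.

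**3. Difference detectable at 80% power, in SD units.** (1.960 + 0.842) × √(2 / 43.1) = 0.60.

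**4. What this implies for HADS.** SD = 3 / 0.6037 = 4.97.

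Forward check with an assumed SD of 5:

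- per arm: 2 × (2.802 × 5 / 3)² = 43.6, rounded up to 44, so 88 in total;
- with clustering: 88 × 1.3 = 114.4, rounded up to 115;
- with loss: 115 / 0.8 = 144, or 115 × 1.2 = 138.

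Sensitivity to the assumed SD, dividing by 0.8 for loss:

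| Assumed HADS SD | Total required |
|---|---|
| 4.5 | 118 |
| 4.95 | 140 |
| 5 | 144 |
| 5.5 | 173 |

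So 140 is coherent for HADS at an SD near 5.

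**5. What 140 gives for another continuous score.** Assume the same design effect and the same loss. Power = Φ(d × √(43.1 / 2) − 1.960), where d is the effect in SD units.

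| Effect (SD units) | Power |
|---|---|
| 0.60 | 80% |
| 0.5 | 64% |
| 0.4 | 46% |
| 0.3 | 29% |
| 0.2 | 15% |

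The HADS figure of 80% carries over to an EQ-5D-5L score only if the effect on that score is also about 0.60 SD. The article assumes no effect for it.

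**The case against.** The best defence is that the label is a slip in a run-together list. The EQ-5D otherwise serves only an exploratory economic aim, the sizing on HADS is coherent, and the analysis section speaks of a single endpoint. That may be so, but nothing in the article corrects the label.

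The defence does rule out several stronger readings that a reader might infer.

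- **Two declared primaries.** HADS is never called primary. There is one labelled primary and a different outcome used for sizing.
- **A 3-point difference that spans the whole HADS scale.** The HADS entry says "The lowest score being 0 and the highest score being 3". Other entries also give a response range: ICECAP-SCM 1 to 4 over seven attributes, TechPH 1 to 5, the 30-item motivation measure 1 to 7. The natural reading is an item range, and the implied SD of about 5 points to a summed score. The wording is loose but does not contradict the sample size.
- **3 points and 25% cannot both be right.** They could: 3 is 25% of a reference mean of 12 (3 / 12 = 0.25). That mean is not given, so the phrase is unclear, not impossible.
- **A false-positive rate of 22.6%.** This is 1 − 0.95⁵, for five independent tests. No section plans a separate test of each EQ-5D-5L dimension.
- **Power and error rate fail for either outcome.** Power for HADS holds if the SD is near 5, and a single endpoint named in advance and tested at 5% keeps its error rate.

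The missing SD and the choice of HADS score may stand in the full protocol, so their absence from an article is not a fault in itself.

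**Conclusion.** The mismatch stands and needs correction. The labelled primary and the outcome behind the sample size are different instruments, the labelled one is not a single score, and the analysis section leaves the endpoint unnamed.

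Its size is the gap between the stated 80% and the power that 140 would give the EQ-5D-5L. That power reaches 80% only at about 0.60 SD, and is 64% at 0.5 SD and 46% at 0.4 SD. These figures rest on the article's 20% loss and design effect of 1.3, both carried over to the EQ-5D-5L, and on a normal approximation for one continuous score. The agreement between 140 and HADS rests on an SD near 5, which was solved back from the total and does not come from the article.

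**What to change.** Issue a dated amendment, before any outcome data are examined by arm, that names one primary outcome as a single score and makes the Participants, Patients and Quantitative data sections agree.

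- **If HADS is intended**, which is the choice consistent with the existing sample size: say which HADS score it is, give the effect once, in points, with the SD that the sponsor originally used (not the value near 5 solved back here), remove the primary label from the EQ-5D-5L entry, and make the EQ-5D-5L a secondary outcome that feeds the QALYs.
- **If the EQ-5D-5L is intended**: define one score, state the effect and SD assumed for it, and report the power that 140 gives for that score in place of the 80% worked out for HADS.

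No new data are needed, because both instruments are already collected from patients and relatives. It is still more than an edit: Data collection and follow-up says that patients and relatives were recruited from September 2021, so the amendment should record when and why the primary outcome was settled. The registry entry, not seen here, should be checked for agreement.
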